## Introduction

1.

Closed reduction is a common method for treating developmental dysplasia of the hip (DDH) in children aged 6–8 months; however, re-dislocation after reduction, avascular necrosis, residual acetabular dysplasia (RAD), and other complications cannot be completely avoided (1). Among these, RAD is the most common complication of DDH closed reduction treatment. A prospective multicenter study conducted by Sankar et al. (2) found that even with stable closed reduction, approximately 11% of children still had residual dysplasia, and long-term follow-up results of a study by Terjesen (3) noted a higher statistic of up to 38%. RAD is the main cause of osteoarthritis (OA) in young adults (4, 5) which often requires total hip replacement (THR). Approximately 9.1% of THR is caused by RAD, and among young adults, this proportion is as high as 21%–29% (6, 7). Therefore, prevention of RAD after DDH treatment and timely correction of RAD are key to long-term prevention of OA.

The causes of RAD in children after closed reduction for DDH are complex. Age, dislocation height, and acetabular index at reduction are commonly used clinical indicators to predict RAD (3, 8, 9), but these factors can only partially explain the causes of RAD from clinical phenomena. Several factors affect the development of the acetabulum after closed reduction. In addition to the genetic quality of DDH, the quality and development potential of the acetabular cartilage, the soft tissue in the acetabulum, and the evolution of the concentric relationship between the acetabulum and femoral head are related to the shaping ability of the hip joint. A relevant understanding of the internal causes of RAD and timely intervention are of clinical significance for the prevention of OA caused by RAD. Previous clinical studies based on indirect radiological observations cannot directly reflect real world practice, in which the non-bone structure and concentric evolution of the hip joint must be considered. Radiological observations can be used to monitor acetabular development; however, they cannot accurately predict RAD (10, 11). Therefore, a method for follow-up observation of hip joint development is warranted to enable better clinical understanding of RAD.

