Magnetic resonance imaging (MRI) can display all bone and non-bone structures of the hip joint from multiple planes; therefore, it is useful for observing development of the acetabulum after closed reduction of DDH. However, MRI is commonly used to evaluate the pathological morphology of DDH before reduction and is seldom used for long-term follow-up (13, 14). In 2020, we published prospective MRI long-term follow-up results after closed reduction of DDH and established that “safety” (a reduction which could be maintained by the abduction of <65°) and “stability” (Ramsey safe zone >30°) are acceptable closed reduction standards (15). Owing to shaping of the pathological structure of soft tissue after reduction, non-concentric reduction of the DDH can gradually achieve concentric reduction. Additionally, we found an interesting phenomenon during follow-up using serial MRI: the inverted limbus was not absorbed overtime; instead, it was compressed into a thin layer of fibrous tissue inter-positioning in the superior joint space (15). Previous radiographic studies have shown that the inverted limbus can be absorbed and can disappear with gradual “docking” of the femoral head after reduction, but this is not the case. Intraoperative arthrography has shown that the inverted limbus is a hypertrophic filling defect with a widening superior joint space (Figure 1A); although this cannot be observed during the course of medium-term follow-ups (Figure 1B), MRI can reveal the residual inverted limbus as a thin layer of hypointense tissue embedded in the superior joint space (Figure 1C), as confirmed during surgery correcting for RAD (Figure 1D). This phenomenon has not been reported previously.

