##### Exclusion criteria

2.2.1.2.

1.Neuromuscular or syndromic DDH;2.Repeated surgical treatment because of re-dislocation, RAD, or other reason after DDH reduction;3.Incomplete imaging data.

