###### Inclusion criteria

2.2.2.1.1.

Inclusion criteria 1–5 are the same as the previously listed inclusion criteria 1–5 (2.2.1.1);

6. More than 1 year after closed reduction;7. Patients aged ≤5 years at follow-up;8. The magnitude of limbus inversion exceeded 32% of the horizontal depth of acetabular roof at follow-up (or the cut-off value obtained in Protocol 2.2.1);9. The acetabular index was ≤30° at follow-up (since an acetabular index>30° usually necessitates pelvic osteotomy).

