##### Research object

2.2.3.1.

In each center, the quality of reduction was first evaluated intraoperatively based on our published “safety and stability” criteria for an acceptable closed reduction (15), i.e., the safe zone >30° during intraoperative inspection and the reduction maintained with the hip in <65° abduction. DDH patients undergoing closed reduction at 6–18 months who satisfied the criteria were selected as participants for observation. The exclusion criteria are the same as those specified in study protocol 2.2.1. In the case of <70° abduction before DDH reduction, percutaneous adductor longus tenotomy was performed. The trail is illustrated in a flowchart as shown in Figure 6.

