##### Statistical analysis

2.2.3.4.

Fisher's precision probability test was used to compare the difference between the sexes and affected sides, using analysis of variance to compare the different ages between the surgical and non-surgical cohorts. Differences in acetabular index was compared using Student's *t*-test. The chi-square test was used to compare IHDI classification, VAS and HHS, and Severin classification at the final follow-up, and analysis of variance was used to compare the MRI T1ρ mapping values, re-dislocation rate, incidence of RAD, and incidence of AVN between the two cohorts.

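### Part 3 takes over the part 1 exclusion for repeat surgery after reduction without a time limit; applied after entry, it would remove treatment failures from the rates that part 3 compares

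*Protocol article*

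**What the plan says.** Part 3 is headed a multicentre prospective cohort study. Under 2.2.3.1 (Research object), reduction quality is judged intraoperatively, and children "who satisfied the criteria were selected as participants for observation". Section 2.2.3.2 allocates them to closed or open reduction from the intraoperative arthrogram, so entry, cohort and index treatment coincide.

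For exclusions, 2.2.3.1 says only: "The exclusion criteria are the same as those specified in study protocol 2.2.1". The list in 2.2.1.2 has three items: neuromuscular or syndromic DDH; "Repeated surgical treatment because of re-dislocation, RAD, or other reason after DDH reduction"; and incomplete imaging data. Part 3 adds no time limit to the second item.

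Follow-up is six-monthly, with further measurements at skeletal maturity (2.2.3.3). Section 2.2.3.4 compares the acetabular index and final Severin class, and also "re-dislocation rate, incidence of RAD, and incidence of AVN between the two cohorts". Acetabular index improvement and Severin class are primary outcomes (2.3.1).

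**The concern.** The exclusion was written for a retrospective study, where a child's later surgical history is already known at selection. It also works in part 2, where entry requires "More than 1 year after closed reduction". In part 3 the surgery that it names would mostly happen after the child has been enrolled and treated, and two of its named causes, re-dislocation and RAD, are outcomes that part 3 compares.

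Such surgery is to be expected. Section 2.2.2.1.1 says that an acetabular index above 30° "usually necessitates pelvic osteotomy", and the Introduction describes residual limbus tissue "as confirmed during surgery correcting for RAD". Children re-operated for RAD would tend to have the worst acetabular index, so the acetabular index and Severin comparisons would lose the same hips.

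Part 3 tests open reduction with limbus excision in infants who already meet the group's criteria for an acceptable closed reduction, and the programme aims to revise those criteria. If failures leave the cohorts, both treatments look better than they are, and the contrast depends on how often each cohort is re-operated as well as on how often it fails.

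**Working it through.** **Plan's own figure.** Part 3 states no sample size and no re-operation rate. The only calculated figure is 67 per group for part 1 (2.2.1.4). It reproduces: difference 21.41 − 18.88 = 2.53°, pooled SD √((3.61² + 4.32²)/2) = 3.98°, two-sided α 0.05 and power 0.9 give 53 per group, and 53/(1 − 0.2) = 66.25, rounded up to 67. This point does not depend on it.

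**Timing of the criterion**

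| Part | Entry | Can the surgery precede entry? |
|---|---|---|
| 1 | Retrospective, more than 5 years of follow-up | Yes, known at selection |
| 2 | More than 1 year after closed reduction | Yes |
| 3 | At the index reduction | Only after an earlier reduction; otherwise it follows entry |

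**Inputs for the illustration**
- True RAD rate p: 11% ("approximately 11% of children still had residual dysplasia") and 38%, the two figures in the Introduction. They describe earlier closed-reduction patients, not part 3 results.
- Share e of RAD cases re-operated and excluded: not in the article; assumed 20%, 50% and 80%.
- Only RAD cases are removed.

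**Formula.** Of a cohort of 1, pe is removed, so the observed rate is p(1 − e)/(1 − pe).

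| True p | e = 20% | e = 50% | e = 80% |
|---|---|---|---|
| 11% | 0.088/0.978 = 9.0% | 0.055/0.945 = 5.8% | 0.022/0.912 = 2.4% |
| 38% | 0.304/0.924 = 32.9% | 0.190/0.810 = 23.5% | 0.076/0.696 = 10.9% |

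**Effect on the comparison**
- Equal exclusion: with true rates of 38% and 11% (27 points apart) and e = 50% in both cohorts, the observed rates are 23.5% and 5.8%, or 17.6 points apart before rounding of the rates.
- Unequal exclusion with no true difference: with e = 30% in one cohort and 60% in the other, a true 11% is observed as 0.077/0.967 = 7.96% and 0.044/0.934 = 4.71%, a false difference of 3.3 points. A true 38% is observed as 0.266/0.886 = 30.0% and 0.152/0.772 = 19.7%, a false difference of 10.3 points.

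Which cohort would be re-operated more often cannot be derived from the article, so the direction is unknown.

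**Acetabular index.** Suppose that one cohort alone loses its highest fraction q. Under normality its mean falls by SD·φ(z)/(1 − q), where z cuts off the upper fraction q. With the part 1 SDs of 3.61° and 4.32°, q = 0.5 × 0.38 = 0.19 gives 1.2° to 1.4°, and q = 0.8 × 0.38 = 0.304 gives about 1.8° to 2.2°. The shift keeps growing with the assumed share, so no upper bound can be given. These SDs also describe the index at final follow-up, whereas the primary outcome is its improvement.

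**The case against.** The strongest reply is that exclusion criteria apply at entry. The sentence stands in the section on selecting participants, and section 4.1 ties the exclusion criteria to who is considered for the study. Nothing in 2.2.3 says that an enrolled child is withdrawn after re-operation, and listing re-dislocation and RAD as comparisons suggests that the authors mean to count failures. The part 3 flow diagram, which might settle this, is not available.

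This stands in part. Removal during follow-up is one of two readings, and under the entry-only reading there is no bias. But the criterion refers to surgery after the reduction, entry is at the reduction, and no wording confines it to earlier surgery or keeps re-operated children in. Centres could apply it differently. The conflict is between a stated eligibility rule and stated outcomes, so it is not a detail left to an analysis plan.

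A reader might go further and infer that in part 3 the repeat surgery can only occur after entry. The article does not support that. Part 3 takes over the part 1 exclusions but not the part 1 inclusion rule of no other treatment before reduction (2.2.1.1). A child re-operated after an earlier reduction and returning for another within 6 to 18 months of age could otherwise qualify, so the criterion can have a legitimate function at baseline.

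It is also fair that the sizes above are conditional: the excluded shares are assumed.

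**Conclusion.** The point holds as a fault in a stated rule: part 3 imports an outcome-related exclusion without a time limit. It does not show that the protocol certainly removes failures. If the criterion is applied after entry, each cohort's RAD rate falls, for example from 38% to 23.5% or from 11% to 5.8% when half of the cases are excluded, and the re-dislocation rate is affected in the same way. The acetabular index and Severin comparisons lose the same hips.

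The downward direction assumes that the excluded children are mainly cases of the outcome in question; re-operation for unrelated reasons would dilute it. The between-cohort distortion has no predictable sign, and the acetabular index shift has no defensible upper bound.

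**What to change.** In 2.2.3.1:
- limit the repeat-surgery criterion to surgery performed before enrolment, that is, before the index reduction;
- apply all imported exclusions at entry only;
- state that re-operation after the index reduction is not a ground for exclusion.

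The criterion should be qualified, not deleted, because it may be the only listed bar to a child already re-operated after an earlier reduction. The imaging criterion can also stay, as an entry check.

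In 2.2.3.4, keep re-operated children in the denominators and count re-operation for re-dislocation or RAD as an event in both cohorts.

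The cost is a few sentences, with no new measurement and no change to a sample size. The downside is that a rule is then needed for radiographs taken after re-operation. Using the last value before re-operation is one option, but it compares children at different ages, so a sensitivity analysis should accompany whichever rule is chosen.

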**Figure 6 F6:**
[figure not shown]
Flow diagram of the multicenter prospective cohort study.

##### Cohort grouping and interventions

2.2.3.2.

For cases meeting the assessment criteria specified in 2.3.1, the labral morphology was further evaluated using intraoperative arthrograms if there was no limbus inversion or if magnitude of the limbus inversion was <32% of the horizontal depth of the acetabular roof (or the cut-off value obtained in 2.2.1). A closed reduction using Spica cast immobilization was then performed to construct the control cohort. If intraoperative evaluation suggested that the magnitude of limbus inversion exceeded the cut-off, open reduction with post-reduction Spica cast immobilization was performed, in which the acetabular soft tissues were removed *via* the bikini incision approach, and the inverted limbus was excised. Patients undergoing open reduction procedures constituted the experimental cohort. Patients in the two cohorts underwent post-reduction cast immobilization for 3 months followed by immobilization with braces for 3 months.

##### Prospective follow-up observation

2.2.3.3.

The control and experimental cohorts were observed radiologically every 6 months during follow-up, and the short-, mid-, and long-term outcomes of hip joint morphological development were compared between the two groups of pediatric patients. Data pooling was performed once every 2 years, and clinical function tests, radiologic measurements, and MRI T1ρ mapping measurements were performed at the stage of skeletal maturity.

##### Statistical analysis

2.2.3.4.

Fisher's precision probability test was used to compare the difference between the sexes and affected sides, using analysis of variance to compare the different ages between the surgical and non-surgical cohorts. Differences in acetabular index was compared using Student's *t*-test. The chi-square test was used to compare IHDI classification, VAS and HHS, and Severin classification at the final follow-up, and analysis of variance was used to compare the MRI T1ρ mapping values, re-dislocation rate, incidence of RAD, and incidence of AVN between the two cohorts.

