##### Statistical analysis

2.2.1.4.

Statistical analysis was performed using SPSS 27.0 software (IBM, SPSS Inc.).
1.To ensure consistency and reliability between multicenter research samples, it is first necessary to conduct a consistency analysis on the structural data, such as age and sex, of the included cases from each center and the International Hip Dysplasia Institute (IHDI) classification using the Cohen's kappa statistic. Simultaneously, the baseline characteristics (such as structural composition and pathological severity) of the included cohorts within each center must be consistent; imbalances in baseline characteristics were corrected by increasing the sample size.2.The included patients were divided into the non-limbus inversion group (A) and the limbus inversion group based on the presence of limbus inversion at closed reduction. The limbus inversion group was then further divided into the RLI group (B) and the resolved inverted limbus group (C) according to the state at final follow-up. A combination consisting of any two of the groups was organized into cohorts. Fisher's precision probability test was used to compare the difference between the sexes and affected sides, using analysis of variance to compare the different ages between the two groups. Differences in acetabular index was compared using Student's *t*-test. Chi-square test was used to compare IHDI classification, VAS and HHS, and Severin classification at the final follow-up, and analysis of variance was used to compare the MRI T1ρ mapping values and the difference in the initial magnitude of limbus inversion between groups B and C, as well as the difference between the initial magnitude of limbus inversion and that at the final follow-up in group B.3.ROC curve analysis was used to predict the cut-off value of the initial magnitude of limbus inversion in the case of persistent RLI as well as calculate its specificity, sensitivity, and statistical significance.4.Sample size calculation.In this study, ossification of the acetabular cartilage was the main observation; thus, improvement of the acetabular index was the most suitable observation indicator. The sample size calculation was based on the previously published acetabular index at the final follow-up in the group with RLI and the group without RLI after closed reduction (21.41°±3.61° and 18.88 ° ± 4.32° in the two groups, respectively) (15). The significance level *α*, the statistical power of the test, the ratio of the sample sizes in the two groups, and the percentage of patients lost to follow-up were set at 0.05, 0.9, 1:1, and 20%, respectively. The minimum sample size for each group was calculated to be 67 cases (134 cases in total). Therefore, at least 67 cases needed to be enrolled in the observation group and the control group, respectively.

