##### Statistical analysis

2.2.2.6.

Fisher's precision probability test was used to compare the difference between the sexes and affected sides, using analysis of variance to compare the different ages between the surgical and non-surgical cohorts. Differences in acetabular index was compared using Student's *t*-test. Chi-square test was used to compare IHDI classification, VAS and HHS, and Severin classification at the final follow-up, and analysis of variance was used to compare the MRI T1ρ mapping values and the incidence of Grade III and Grade IV adverse events.

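### Chi-square is named for the numeric VAS and Harris scores and ANOVA for yes/no incidences; the methods look swapped, and the main cost is lost power on the scores

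*Protocol article*

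**What the plan says.** **Scores.** Sections 2.2.1.4 and 2.2.2.6 state: "Chi-square test was used to compare IHDI classification, VAS and HHS, and Severin classification at the final follow-up". Section 2.2.3.4 says the same in almost identical words. Section 2.2.1.3 describes the VAS as a mark on an unscaled 100-mm line. No cut-points or bands are given there or elsewhere for VAS or HHS. Section 2.3.2 lists both as secondary outcomes.

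**Incidences.** Section 2.2.2.6 states: "analysis of variance was used to compare the MRI T1ρ mapping values and the incidence of Grade III and Grade IV adverse events". Section 2.2.3.4 puts three more events under analysis of variance: "analysis of variance was used to compare the MRI T1ρ mapping values, re-dislocation rate, incidence of RAD"; the list of events in full is "re-dislocation rate, incidence of RAD, and incidence of AVN between the two cohorts". Section 2.3.1 lists AVN as a primary outcome.

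**Change within group B.** Section 2.2.1.4, item 2, includes among the ANOVA comparisons "the difference between the initial magnitude of limbus inversion and that at the final follow-up in group B". It does not say which form of ANOVA is meant.

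**Other tests.** The same paragraphs use Fisher's test for sex and affected side, and Student's t-test for the acetabular index.

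**The concern.** Chi-square compares proportions across categories, and ANOVA compares means. The article gives the category test to scores that have no categories, and the means test to events that each patient either has or does not have. These are stated rules, repeated across the sub-studies, so they are not details left to a fuller document.

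Two things are at stake:
- **Function and pain.** Used literally, chi-square treats every distinct score as its own unordered category. Most cells are then nearly empty, and the size and direction of differences are ignored.
- **Safety of the added open procedure.** AVN, re-dislocation and Grade III/IV events may be few. With few events, the choice between an approximate and an exact test can decide which side of 0.05 a result falls on. The ANOVA F-test also does not deliver a risk estimate with an interval suited to small counts.

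There is a smaller point on group B. Initial and final inversion are measured in the same patients, and the text does not say that the comparison is paired.

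**Working it through.** **1. The plan's own figure, and the group size used below.** Inputs from 2.2.1.4: acetabular index "21.41°±3.61° and 18.88 ° ± 4.32° in the two groups, respectively"; significance level, power, allocation ratio and loss "were set at 0.05, 0.9, 1:1, and 20%, respectively".
- Difference = 21.41 − 18.88 = 2.53. Pooled SD = √((3.61² + 4.32²)/2) = 3.98.
- n = 2(1.960 + 1.282)² × 3.98²/2.53² → 53 per group (two-sided).
- With 20% loss: 53/0.8 = 66.25 → 67, the stated size.

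The figure reproduces. It rests on the acetabular index and does not depend on the tests at issue. Sections 2.2.2 and 2.2.3 state no size, so 53 per group is borrowed from study 1 as an assumption.

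**2. Scores.** The documents give no distribution for either score. Assumed: whole-number scores capped at 100, mean 90 vs 87, SD 6, 53 per group. Simulated power at 0.05:

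| Test | Power |
|---|---|
| Chi-square on raw values | about 10% |
| Chi-square on four assumed bands (cuts at 70, 80, 90) | about 48% |
| Wilcoxon rank-sum | about 70% |
| t-test | about 72% |

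On raw values about 96% of expected cell counts are below 5. With no true difference, the raw chi-square rejects in about 2% of trials, so the fault is lost power and not excess false positives.

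**3. Incidences.** For two groups and 0/1 data with N patients in all, the ANOVA statistic is a function of Pearson's chi-square (X²):

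F = (N − 2)X²/(N − X²).

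Take 4/53 vs 0/53, so N = 106 and the pooled proportion is 4/106 = 0.0377.
- X² = (4/53)²/(0.0377 × 0.9623 × 2/53) = 4.157
- F = 104 × 4.157/(106 − 4.157) = 4.245

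| Events per 53 | ANOVA p | Pearson p | Fisher p |
|---|---|---|---|
| 4 vs 0 | 0.042 | 0.041 | 0.118 |
| 5 vs 0 | 0.022 | 0.022 | 0.057 |
| 7 vs 1 | 0.027 | 0.027 | 0.060 |

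Exact enumeration of all tables gives the actual type I error at 53 per group. The event rates are assumed, except that 38% is the upper RAD figure in the Introduction:

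| Event rate | ANOVA | Fisher |
|---|---|---|
| 2% | 0.015 | 0.0005 |
| 5% | 0.044 | 0.008 |
| 10% | 0.049 | 0.019 |
| 20% | 0.050 | 0.030 |
| 38% | 0.053 | 0.033 |

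ANOVA and uncorrected Pearson disagree at 0.05 in 4 of the 54 × 54 = 2,916 possible tables at 53 per group, and in none at 54 or 67.

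**4. Group B.** If pairing were ignored, the standard error would be too large by a factor 1/√(1 − ρ), where ρ is the within-patient correlation. At an assumed ρ = 0.5 this is 1.41. In simulation with 54 patients, type I error would then be 0.006, and power for a 0.4 SD change would be 56% instead of 82%. This applies only if the ANOVA is unpaired. A repeated-measures ANOVA with two time points is the paired t-test.

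**The case against.** A reader might infer that the plan gives wrong p-values throughout, including for the primary outcome AVN. The documents and the arithmetic do not support that. For two groups, ANOVA on 0/1 data is almost the same test as Pearson's chi-square, with type I error near or below 5%. The gap at 4 vs 0 is between an exact and an approximate test, and ordinary chi-square falls on the same side as ANOVA. Fisher's test is itself conservative at these counts. This objection stands.

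A reader might also infer that group B is to be analysed as independent groups. Section 2.2.1.4 says only analysis of variance, which may mean repeated measures. An unpaired analysis would in any case be conservative under positive correlation. What remains is that the form is not stated.

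Calling chi-square on Severin class an error would also go too far. It is a valid test that ignores the order of the classes, so an ordinal method is a gain in efficiency.

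Finally, VAS and HHS are secondary outcomes, and the authors may intend to band them. Bands would reduce the loss but not remove it (about 48% vs 70% in the example), and the article defines none.

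**Conclusion.** The concern holds in a limited form, at moderate severity. The clear fault is chi-square for VAS and HHS in all three sub-studies. Taken literally, it loses most of the power to detect a difference: about 10% against 70% in the example. Those figures depend on the assumed distribution, shift and group size, and on chi-square being run on ungrouped values.

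ANOVA for AVN, re-dislocation, RAD and Grade III/IV events is the wrong method to name. Its p-values nonetheless track Pearson's chi-square closely, and it matters mainly when events are sparse and for the effect estimate reported. The documents give no AVN or adverse-event rate, so how sparse these events will be is unknown.

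The group B comparison needs its paired form stated. The 67 per group and the acetabular index t-test are not affected.

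**What to change.** - **2.2.1.4, 2.2.2.6 and 2.2.3.4:** compare VAS and HHS by the Wilcoxon rank-sum test or a linear model.
- **2.2.2.6 and 2.2.3.4:** compare Grade III/IV events, re-dislocation, RAD and AVN by Fisher's exact test, already used for sex and side, or by a logistic model. Report the risk difference with a 95% CI.
- **2.2.1.4:** state that initial versus final inversion in group B is a paired comparison, and name the method (paired t-test, signed-rank test or repeated-measures ANOVA).
- **Optional:** use a rank-sum test or proportional-odds model for Severin class.

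The cost is analysis wording only, with no new data and no change in sample size. The change is best made and dated before outcomes are compared by group.

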##### Randomized blocks and interventions

2.2.2.2.

A randomized trial study design was the most appropriate approach to observe the efficacy of surgical intervention, with blinding techniques used during statistical analysis of the data. A double-blind study was not feasible because the surgeon was required to provide detailed information on the surgical regimen. The researchers in each center divided the RLI participants into two study cohorts based on the randomized block design, i.e., the surgery and non-surgery groups. After informed consent was obtained from the guardians of patients in the surgery group, clearance of the inverted limbus *via* arthrotomy was performed.

All surgeries were performed by pediatric hip joint surgeons with senior job titles *via* a bikini incision, and the inverted limbus tissue embedded between the acetabulum and femoral head was excised after arthrotomy without damaging the limbus-cartilage complex. After surgery, casts or braces were applied to immobilize single hips in abduction for 4 weeks and the patients gradually resumed walking after removal of external fixators. No special rehabilitation therapy was administered.

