##### Adverse events observation

2.2.2.4.

Complications and adverse events in the surgical treatment group were recorded and classified according to the adverse event classification system described by Sink et al. (DOI:10.1007/s11999-012-2343-2). Grade I: no clinical relevance and no need to change routine postoperative care; Grade II: resolving spontaneously after simple outpatient management or outpatient observation; Grade III: requiring hospitalization or surgical treatment before resolution; Grade IV: chronic impairment of body functions. Grade III and IV events were included in the analysis of results.

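### Yes/no incidences, including the primary outcome AVN, are assigned to analysis of variance; use a test for proportions and an interval for the risk difference

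*Protocol article*

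**What the plan says.** The protocol article assigns one method to continuous and yes/no outcomes alike in two places.

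- **Part 3, prospective cohort study (2.2.3.4):** analysis of variance is named for the T1ρ values and, in the same list, for "re-dislocation rate, incidence of RAD, and incidence of AVN between the two cohorts".
- **Part 2, randomised study (2.2.2.6):** "analysis of variance was used to compare the MRI T1ρ mapping values and the incidence of Grade III and Grade IV adverse events".

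Both paragraphs treat other categorical variables differently: "Fisher's precision probability test was used to compare the difference between the sexes and affected sides", with chi-square for the IHDI and Severin classifications. Section 2.3.1 lists AVN among the primary outcomes.

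The two parts form their groups differently. In part 3 the limbus-inversion cut-off decides (2.2.3.2): "If intraoperative evaluation suggested that the magnitude of limbus inversion exceeded the cut-off, open reduction with post-reduction Spica cast immobilization was performed". The cohort sizes are therefore whatever the cut-off produces. In part 2 the centres (2.2.2.2) "divided the RLI participants into two study cohorts based on the randomized block design, i.e., the surgery and non-surgery groups"; the allocation ratio is not stated. No confidence interval is named for any of these incidences.

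**The concern.** Re-dislocation, RAD, AVN and a Grade III or IV event either occur in a patient or do not. Such an outcome has variance p(1-p), so two groups with different rates have different variances. Analysis of variance estimates one common variance for both. With unequal group sizes, that pooled estimate gives the wrong standard error for the difference in rates.

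At stake is how precisely the plan can report one primary outcome and the main complication rates after open reduction and limbus excision. The text is also inconsistent: baseline sex and side receive a test suited to categories, while the complication rates do not.

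**Working it through.** **The plan's own figure.** The article states no size, rate or interval for these incidences. Its only computed figure is the part 1 sample size (2.2.1.4), which reproduces for two-sided alpha 0.05: (1.960 + 1.282)² × (3.61² + 4.32²) / (21.41 - 18.88)² = 10.51 × 31.69 / 6.40 = 52.03, so 53; 53 / 0.8 = 66.25, so 67 per group. It serves here only as a guide to plausible group sizes.

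**Inputs.** The rates 11% and 38% are the two published RAD figures in the Introduction, used as illustrations. All other rates, and every pairing of sizes, are assumptions.

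**Step 1: standard error.** For groups n1, n2 with rates p1, p2 and N = n1 + n2:

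- pooled SE = √{[n1·p1(1-p1) + n2·p2(1-p2)]/N × (1/n1 + 1/n2)}
- true SE = √{p1(1-p1)/n1 + p2(1-p2)/n2}

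For 5% of 134 against 20% of 40, the variances are 0.0475 and 0.16.

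- Pooled: (134 × 0.0475 + 40 × 0.16)/174 = 0.0734; times (1/134 + 1/40) = 0.0325 gives 0.00238, so SE 0.0488.
- True: 0.0475/134 + 0.16/40 = 0.00435, so SE 0.0660.
- Ratio: 0.74. The interval is too narrow.

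Exchanging the rates exchanges the two standard errors: the ratio is 1.35 and the interval is too wide.

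**Step 2: coverage of 95% intervals**, by exact enumeration of both binomials. The ANOVA interval is difference ± t(0.975, N-2) × pooled SE, with the SE estimated from each data set.

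| Groups | SE ratio | ANOVA | Newcombe |
|---|---|---|---|
| 5% of 134 v 20% of 40 | 0.74 | 84.1% | 95.1% |
| 20% of 134 v 5% of 40 | 1.35 | 99.0% | 95.8% |
| 3% of 134 v 10% of 40 | 0.75 | 84.7% | 95.8% |
| 10% of 134 v 3% of 40 | 1.33 | 98.7% | 96.6% |
| 5% of 134 v 15% of 67 | 0.86 | 90.6% | 95.7% |
| 15% of 134 v 5% of 67 | 1.17 | 97.9% | 95.8% |
| 11% of 100 v 38% of 34 | 0.81 | 88.5% | 95.1% |
| 38% of 100 v 11% of 34 | 1.23 | 98.5% | 95.2% |
| 11% of 67 v 38% of 67 | 1.00 | 95.1% | 95.2% |

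The interval is too narrow when the smaller cohort has the larger p(1-p), too wide when the larger cohort has it, and about right with equal sizes.

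**Step 3: the test.** On 0/1 data in two groups, F = (N-2)X²/(N-X²), where X² is the uncorrected Pearson chi-square. For 0/134 against 2/40, X² = 6.78 and F = 172 × 6.78/(174 - 6.78) = 6.97.

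| Data | ANOVA p | Chi-square p | Fisher p |
|---|---|---|---|
| 0/134 v 2/40 | 0.0090 | 0.0092 | 0.052 |
| 0/67 v 4/67 | 0.0426 | 0.0423 | 0.119 |

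With equal true rates the F-test rejected 3.8% (5%, 134 v 40), 4.0% (3%, 134 v 40), 4.3% (5%, 134 v 67), 4.7% (5%, 67 v 67), 5.1% (11%, 34 v 100) and 2.4% (2%, 67 v 67). Nominal is 5%. Fisher's test rejected 1.3% at 5% and 0.45% at 3%, both for 67 v 67.

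**The case against.** **The p-values are close to those of an acceptable test.** This stands. When the rates are equal the variances are equal too, so unequal variance does not upset the test under the null. A reader might infer from the two sparse examples that ANOVA produces false signals of harm. The calculations do not support that: chi-square gives nearly the same p-values as ANOVA, and the gap to Fisher's test is mostly Fisher's conservatism.

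**The plan names no interval.** Also true. The coverage argument concerns whatever interval an ANOVA output would supply if an effect estimate were reported. It is not a criticism of an interval the plan has specified.

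**The direction of the error is unknown.** A reader might infer that the intervals would be too narrow. The article does not say which part 3 cohort will be smaller or have the higher rate, so they could as easily be too wide.

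**Part 2 is barely touched.** Randomised blocks with equal arms would keep coverage near 95%, although the ratio is not stated. Section 2.2.2.4 raises a separate difficulty for that comparison: "Complications and adverse events in the surgical treatment group were recorded and classified". It describes no such recording for the non-surgery group, and a change of test would not supply a comparator.

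**A better test does not make part 3 causal.** Its cohorts differ by design in limbus inversion, so no choice of test lets these rates alone show whether surgery harms hips.

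What survives is that the stated method is not meant for these outcomes and departs from the document's own practice for categorical data.

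**Conclusion.** The point holds as a wrongly stated method of moderate severity. Analysis of variance is assigned to four yes/no incidences, one of them a primary outcome. Type I error is not materially inflated in the cases run. Any interval from the pooled variance is unreliable when part 3 sizes and rates differ: coverage ran from about 84% to about 99% for a nominal 95%, against 95% to 97% for Newcombe. These figures rest on assumed cohort sizes and rates. They show that the error can go either way, not which way it will go. A must-fix rating would require distorted tests or a known direction of error, and the article supports neither.

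**What to change.** In 2.2.2.6 and 2.2.3.4, remove re-dislocation, RAD, AVN and Grade III-IV adverse events from the ANOVA list. State that each is compared by a chi-square test, or by Fisher's exact test when expected counts are small, and reported as a risk difference with a Newcombe score 95% interval. T1ρ values can stay where they are.

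The cost is one sentence in each section, with no change to data collection or sample size. The drawback is Fisher's conservatism with few events, which makes a harm signal harder to detect: power is 75% against 80% for chi-square with 5% of 134 v 20% of 40, and 40% against 47% with 3% of 134 v 10% of 40. That is a reason to keep Fisher's test for small expected counts and to read the interval alongside the p-value.
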